## Abstract

**Introduction:**

There are 3.9 million people in the UK with diabetes. Sarcopenia, increased frailty and loss of independence are often unappreciated complications of diabetes. Resistance exercise shows promise in reducing these complications in older adult diabetes patients. The aim of this feasibility randomised controlled trial is to (1) characterise the physical function, cardiovascular health and the health and well-being of older adults with mild frailty with/without diabetes treated with insulin, (2) to understand the feasibility and acceptability of a 4-week resistance exercise training programme in improving these parameters for those with diabetes and (3) to test the feasibility of recruiting and randomising the diabetic participant group to a trial of resistance training.

**Methods and analysis:**

Thirty adults aged ≥60 years with insulin-treated diabetes mellitus (type 1 or 2), and 30 without, all with mild frailty (3–4 on the Rockwood Frailty Scale) will be recruited. All will complete blood, cardiovascular and physical function testing. Only the diabetic group will then proceed into the trial itself. They will be randomised 1:1 to a 4-week semisupervised resistance training programme, designed to increase muscle mass and strength, or to usual care, defined as their regular physical activity, for 4 weeks. This group will then repeat testing. Primary outcomes include recruitment rate, attrition rate, intervention fidelity and acceptability, and adherence to the training programme. A subset of participants will be interviewed before and after the training programme to understand experiences of resistance training, impact on health and living with diabetes (where relevant) as they have aged. Analyses will include descriptive statistics and qualitative thematic analysis.

**Ethics and dissemination:**

The North East-Newcastle and North Tyneside 2 Research Ethics Committee (20/NE/0178) approved the study. Outputs will include feasibility data to support funding applications for a future definitive trial, conference and patient and public involvement presentations, and peer-reviewed publications.

**Trial registration number:**

ISRCTN13193281.

Strengths and limitations of this studyThis is a novel study using mixed methods to examine the feasibility of carrying out a larger trial of a gym-based resistance exercise training programme with older, mildly frail adults with insulin-treated diabetes.A series of in-depth qualitative interviews will generate a better understanding of the barriers and facilitators to resistance-based exercise for this important patient group, where early intervention is key.This study is not intended to be a definitive trial, however, a mixed-methods approach will explore the impact of the training programme on various clinical outcomes and exercise experiences.As the study is limited to the North East of England, the sociodemographic characteristics of participants may differ to the population of the wider UK and other Western countries.

## Introduction

### Background

There are around 425 million people with diabetes worldwide, and by 2040 it is predicted that 1 in 10 people globally with have diabetes.^1^ In the UK, there are around 4 million people living with diabetes^2^ (90% type 2, 8% type 1, 2% other) with a further 1 million with undiagnosed diabetes. The prevalence of diabetes increases sharply with age, with 17.4% of those aged over 65 having diabetes, compared with 2% of those aged 16 to 44 in England.^3^ All of those with type 1 diabetes require insulin treatment, and most of those with type 2 diabetes will eventually also require insulin treatment.^4 5^ Diabetes represents >10% of the National Health Service (NHS) budget in direct treatment costs.^6^ Modern advances in diabetes treatment mean that people with diabetes are living longer,^7^ even with the presence of the microvascular and macrovascular disease associated with long-term diabetes.

With an ageing population of people living with diabetes, it is important that strategies for improving both health, quality of life, and reducing treatment burden are identified. Long-term insulin treatment for diabetes is, however, associated with detrimental effects to health including hypoglycaemia and weight gain,^8^ and may adversely affect muscle health.^9^ Sarcopenia in particular leads to an increased risk of frailty, falls, physical disability, chronic metabolic disease and mortality.^10 11^ The prevalence of frailty in older people with diabetes has been reported as ~32%–48%, which is significantly higher than that of 5%–10% in older persons without diabetes.^12 13^ Recent studies have also demonstrated an increased risk of osteoporosis and fracture in older people with diabetes, compared with age matched non-diabetes controls.^14 15^ Thus long-term diabetes and long-term insulin treatment, hypoglycaemia and age related physical decline, may carry an additional burden for those living with insulin treated diabetes in later life.

Physical activity and exercise interventions have been shown to improve outcomes associated with frailty and sarcopenia (such as muscle mass, muscle force production, cardiorespiratory fitness).^16^ However, these interventions are not straightforward in people with insulin treated diabetes due to the risk of hypoglycaemia.^17^ Aerobic exercise increases insulin sensitivity, changes the absorption and action of the injected insulin and increases metabolic rate dramatically.^18 19^ Under these conditions, in a person without diabetes, the insulin concentrations would drop dramatically during and after exercise, however, in those with diabetes this is not possible (as the insulin is injected), and thus increases the risk of dangerously low blood glucose occurring. Nearly two-thirds of those with type 1 diabetes do not engage in any physical activity,^20^ commonly due to fear of exercise-induced hypoglycaemia.^21^

Established insulin-treated non-obese type 2 diabetes shares many characteristics with type 1 diabetes, due to relatively greater insulin deficiency and lower insulin resistance than in type 2 diabetes associated with obesity. This includes intrinsic glucose variability with higher risk of impaired awareness of hypoglycaemia,^22 23^ including severe events requiring assistance from others in treatment.^24^ We hypothesise that mild frailty may have a comparable impact in type 1 diabetes and insulin-treated type 2 diabetes where body mass index (BMI) is <30 kg/m^2,^ with potentially comparable impacts of resistance exercise training.^25^

Resistance-based exercise, that is, repeated intense muscle contractions of isolated parts of the body against a fixed load, is associated with less fluctuation in blood glucose than aerobic exercise.^26–28^ Resistance exercise is a potent stimulus for improving (1) muscle mass, (2) muscle strength and power, (3) bone health and (4) physical function, such as stair climbing.^29 30^ Existing studies have shown resistance training to be a useful exercise modality in older, non-frail type 1 and type 2 diabetes patients.^31–33^ It is also the modality of exercise with the most evidence for improving outcomes in older people with sarcopenia or frailty,^34 35^ and generally well tolerated by this group.^36^ However, data for its use in older people with diabetes are scant. As resistance training potentially carries less risk of blood glucose fluctuation to those with diabetes, due to differing hormonal responses to aerobic exercise, it has potential to be a preferred modality of exercise for this group, and may help sustain long-term engagement.^26–28^

Given the increasing ageing diabetes population, and the increased risk of sarcopenia and frailty in this group, it is important to provide lifestyle related interventions, such as resistance training, to improve the quality of life of older people living with diabetes.^37^ At present there is limited information on the physical function of older people with diabetes compared with those without diabetes, as well as how acceptable or feasible a resistance training intervention would be in this group.

Resistance exercise training appears to be a promising intervention to improve the health of those living with insulin treated diabetes, particularly those who are older. However, we have a limited understanding of what form such a resistance training programme might take, and how and to what extent it will improve health.

### Aims and objectives

The purpose of this baseline case–control descriptive observational study and subsequent feasibility trial is to characterise the physical function, cardiovascular health, and the health and well-being of older people with mild frailty and with/without insulin-treated diabetes, and to test the feasibility of conducting a trial of resistance training in improving these parameters, and the acceptability of regular resistance exercise as a modality to improve health outcomes in older people with insulin treated diabetes.

## Methods and analysis

### Study design

This is a single-centre interventional feasibility randomised controlled trial with an associated baseline case–control descriptive observational component, and a qualitative and process evaluation component, conducted in Newcastle upon Tyne, England. Thirty participants with insulin treated diabetes and mild frailty, and thirty without diabetes will be recruited. All participants will be aged ≥60. All participants will undergo blood and physical testing, for the baseline case–control component. The diabetic participants will then go forward into the trial. They will be randomised 1:1 to the intervention group, which is a 4-week programme of supervised resistance exercise training, or to the control group; to carry on with any usual activity as normal. The current version of the protocol is V.3.

### Exclusion and inclusion criteria

Inclusion criteria for diabetes group (n=30):

Adults ≥60 years.Type 1 diabetes OR type 2 diabetes treated with exogenous insulin.BMI <30 in participants with type 2 diabetes.Rockwood Clinical Frailty Score of 3 or 4.

Inclusion criteria for non-diabetes group (n=30):

Adults ≥60 years.Rockwood Clinical Frailty Score of 3 or 4.

Exclusion criteria for all groups:

History of myocardial infarction, stroke, renal failure, severe hypertension or liver disease in the last 12 months.Unsuitable for the intervention due to limiting musculoskeletal problems.Inability to give written informed consent.

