### Data analysis plan

#### Quantitative analysis

This is a feasibility study to inform a larger trial and no hypothesis testing will be conducted. Consequently, quantitative data analysis will be descriptive. Mean, SD, range and 95% CI will be assessed on all quantitative data to assess response rates, numbers of individuals consented and randomised, retention rate, fidelity to the intervention, and participation in the training programme and qualitative interviews. The same descriptive methods will be used to report questionnaire and assessment data at baseline and 5 weeks. Statistical analyses will be conducted using IBM SPSS Statistics V.22 software.

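### The BMI cap applies to type 2 cases only, so the baseline contrast with the non-diabetes group, above all in body composition, can partly reflect eligibility rather than diabetes

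*Protocol article*

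**What the plan says.** Under Exclusion and inclusion criteria, the diabetes group needs age 60 or over, Rockwood 3 or 4, and "Type 1 diabetes OR type 2 diabetes treated with exogenous insulin", with one further limit: "BMI <30 in participants with type 2 diabetes". Type 1 cases have no BMI limit. The non-diabetes list contains only the age and Rockwood criteria. The exclusions common to all groups concern recent major illness ("History of myocardial infarction, stroke, renal failure, severe hypertension or liver disease in the last 12 months"), limiting musculoskeletal problems and inability to consent; none mentions BMI.

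The Background gives the reason for the cap: non-obese insulin-treated type 2 diabetes is held to resemble type 1. It does not discuss what the cap does to the comparison with people without diabetes.

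That comparison is a declared purpose. Aims and objectives calls the study a "baseline case–control descriptive observational study" followed by a feasibility trial, and Study design states: "Thirty participants with insulin treated diabetes and mild frailty, and thirty without diabetes will be recruited". Physical function lists height, weight, waist, percentage body fat and percentage fat-free mass among the baseline measures. Under Quantitative analysis, "quantitative data analysis will be descriptive": means, SDs, ranges and 95% CIs, with no hypothesis tests and no adjustment mentioned.

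**The concern.** One part of the diabetes group is truncated on BMI and the comparison group is not. Weight, waist and body fat are close relatives of BMI, so truncation in one group moves the contrast in these measures whether or not diabetes has any bearing on them. A descriptive analysis does not remove this, because an unadjusted mean with its CI carries the selection in full.

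The Background names limited information on physical function in older people with diabetes, compared with those without, as a gap. The 30 participants without diabetes do not enter the randomised part; apart from the interviews, they are there for this contrast. A reader of the results could take a lower, or an absent, difference in body fat as a feature of insulin-treated diabetes when the entry rule produced part of it.

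**Working it through.** The article gives no figure to reproduce: it reports no sample size calculation, SD or BMI distribution. The check asks how large an artefact the cap could create.

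**Inputs from the article.** BMI below 30 for type 2 cases only; 30 participants per group.

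**Assumptions (not in the article).** Uncapped BMI is normal with the same mean and SD in both populations; mean 27 to 29, SD 4 to 5 kg/m². The share of cases with type 2 diabetes, w, is unknown and is varied from 0 to 1.

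**Step 1: shift in type 2 cases.** For a normal distribution cut off above at 30, with z = (30 − mean)/SD, the mean falls by SD × φ(z)/Φ(z).

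| Mean, SD | z | φ(z)/Φ(z), shift in SD | Shift, kg/m² |
|---|---|---|---|
| 27, 4 | 0.75 | 0.39 | 1.56 |
| 27, 5 | 0.60 | 0.46 | 2.30 |
| 28, 5 | 0.40 | 0.56 | 2.81 |
| 29, 5 | 0.20 | 0.68 | 3.38 |

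**Step 2: shift in the whole diabetes group.** This is w times the figure above. At mean 28, SD 5, it is 0, 0.7, 1.4, 2.1 and 2.8 kg/m² for w = 0, 25, 50, 75 and 100%. At w = 50%, the range over the table is 0.8 to 1.7 kg/m², or about 0.19 to 0.34 SD.

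**Step 3: precision of the comparison.** The 95% half-width for a difference of two means, 30 v 30, is 1.96 × √(2/30) = 0.51 SD (0.52 with the t quantile). This takes a common SD; the cap also narrows the spread in type 2 cases, so it is approximate.

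**Step 4: sensitivity.** Widening the assumptions to means of 26 to 30 and SDs of 4 to 6 gives 0.29 to 0.80 SD if all cases are type 2 (1.2 to 4.8 kg/m²), and 0.6 to 2.4 kg/m² if half are.

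**Step 5: other outcomes.** Steps 1 to 4 concern BMI itself. For an outcome with correlation r with BMI, the induced shift is roughly r times the BMI shift in SD units, hence smaller. The article gives no such correlations, so no figure can be put on gait, strength, blood pressure or lipids.

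**The case against.** The strongest reply has four parts.

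- **The direction is not settled.** The calculation assumes one shared uncapped BMI distribution. The Background links long-term insulin to weight gain and mentions type 2 diabetes associated with obesity. If uncapped type 2 cases would be heavier than the comparison group, the cap may narrow a BMI gap instead of opening one. This stands: the artefact is possible, and its sign and size are conditional.
- **The mix is unknown.** At an even mix, the shift is below the half-width of 0.51 SD; it reaches that size only when most cases are type 2. This also stands.
- **The cap is deliberate and the component descriptive.** True, but the stated reason concerns likeness of type 2 to type 1, and description still invites a group contrast.
- **An analysis plan or Figure 1 may deal with it.** Neither is shown, and the figure's caption does define BMI. What remains is that the article's own criteria create the asymmetry and its analysis section does not address it.

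Stronger readings are tempting but unsupported.

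- A reader might infer that someone with tablet-treated diabetes could enter the comparison group, since no listed criterion says otherwise. But the list is headed as being for the non-diabetes group, and Study design specifies people without diabetes. Only the wording of the aim, "older people with mild frailty and with/without insulin-treated diabetes", is looser.
- A reader might worry about undiagnosed diabetes. Take the Background's 4 million diagnosed, 1 million undiagnosed and 17.4% prevalence over 65, treated as diagnosed. Then 0.174/4 = 0.0435, and 0.0435/0.826 = 0.053, about 1.6 of 30. That would shrink a true 0.5 SD contrast by about 0.03 SD, which is negligible here.
- A reader might fault the lack of age and sex matching or adjustment. Matching is a trade-off in a small feasibility study, and adjustment may sit in an analysis plan.
- A reader might extend the point to the trial. The cap acts before randomisation and equally on both arms, so it does not reach the randomised comparison.

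**Conclusion.** The point holds as a minor one, for the baseline component only. The entry rule is asymmetric, and the article describes no summary that would separate its effect from that of diabetes. On the assumption of a shared BMI distribution with mean 27 to 29 and SD 4 to 5, the cap lowers mean BMI by 1.6 to 3.4 kg/m² (0.39 to 0.68 SD) in type 2 cases. Against a half-width of about 0.51 SD, that can be as large as the precision of the comparison when nearly all cases are type 2, and it vanishes when all are type 1. The concern is firmest for weight, waist and percentage body fat. For function and cardiovascular measures it is a possibility without an established size or direction. It cannot be said that the baseline comparison is distorted, only that it can be.

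**What to change.** Alongside the planned summaries:

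1. Report the baseline differences between the groups with 95% CIs, restricted to participants with BMI <30 in both groups. This is estimation and fits the decision not to test hypotheses.
2. Show the diabetes group by diabetes type. Type 1 cases and the non-diabetes group are both uncapped, so that contrast is free of the asymmetry.
3. Align the aim's wording on insulin-treated diabetes with the Study design wording, so that the comparison group is plainly people without diabetes.

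Height, weight and diabetes type are already collected, so no new measurement or change to recruitment is needed. The cost is precision and scope. At an assumed mean of 28 and SD of 5, about 34% of the comparison group would have BMI 30 or more, leaving about 20 of 30. If all cases are type 2, the half-width becomes 1.96 × √(1/30 + 1/20) = 0.57 SD. If all are type 1 with the same BMI distribution, about 20 v 20 remain and it is 1.96 × √(2/20) = 0.62 SD. The restricted estimates also describe non-obese people only, which is why they should accompany the full summaries and not replace them.

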##### Physical function

Body composition: height, weight, waist circumference, % body fat and % fat free mass using bioelectrical impedance analysis (SECA 515 Body Composition Analyser).Isometric strength: a torque and strain gauge will be used to assess the force capability of the participants’ lower limbs. This test involves maximally extending the leg against an immovable strain gauge, this allows for the calculation of peak force and time-course changes in force.Isometric strength: a torque and strain gauge will be used to assess the force capability of the participants’ lower limbs. This test involves maximally extending the leg against an immovable strain gauge, this allows for the calculation of peak force and time-course changes in force.Gait speed: using digital timing gates, the participants will be required to complete three 4 m walking tests, to assess the normal walking speed of the participants.Timed Sit to stand: participants will sit on a chair and complete five stand and sit movements without use of the arms.

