### Secondary outcomes

#### Clinical and physical outcomes

Body composition measured using height, weight, waist circumference, percentage body fat and percentage fat-free mass using bioelectrical impedance analysis at baseline and 5 weeks.Isometric strength measured using a torque and strain gauge at baseline and 5 weeks.Handgrip strength measured using a digital handgrip dynamometer at baseline and 5 weeks.Gait speed measured using three 4 m walking tests on digital timing gates at baseline and 5 weeks.Timed sit to stand, measured using five sit-to-stand movements at baseline and 5 weeks.Cardiovascular health measured using resting blood pressure, HbA1c, blood lipid profile, and inflammatory cytokines at baseline and 5 weeks.Instances of hypoglycaemia, measured weekly from baseline, obtained using patient self-report.

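### The BMI limit applies to type 2 participants only, so the baseline comparison with people without diabetes mixes diabetes with an eligibility rule

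*Protocol article*

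**What the plan says.** Under Exclusion and inclusion criteria, the diabetes group is defined by age, a Rockwood score of 3 or 4, "Type 1 diabetes OR type 2 diabetes treated with exogenous insulin", and "BMI <30 in participants with type 2 diabetes". The non-diabetes group has only the age and Rockwood criteria. The exclusions common to all groups do not mention BMI.

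Study design states that "Thirty participants with insulin treated diabetes and mild frailty, and thirty without diabetes will be recruited", and that "All participants will undergo blood and physical testing, for the baseline case–control component". Aims and objectives makes describing older people with and without insulin-treated diabetes a stated purpose. Body size is part of that description: the Physical function list opens with "Body composition: height, weight, waist circumference, % body fat and % fat free mass using bioelectrical impedance analysis", and body composition appears again among the Clinical and physical outcomes.

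The Background gives the reason for the limit. Non-obese insulin-treated type 2 diabetes is held to resemble type 1, so frailty and training may act comparably in the two. Quantitative analysis plans descriptive statistics with 95% confidence intervals and no hypothesis tests. It mentions no restriction, matching or adjustment for BMI.

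**The concern.** The rule removes the upper part of the BMI distribution from the type 2 members of one group and from nobody in the other. Weight, waist and percentage body fat are themselves described in the baseline comparison. Gait speed, sit-to-stand time, blood pressure and lipids plausibly depend on body size as well. The Background reason concerns likeness within the diabetes group and gives no ground for leaving the comparison group open.

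At stake is the first stated aim, and the only use made of the comparison group's blood and physical tests. A reader of the baseline tables could attribute to diabetes, or to its absence, a difference that eligibility produced. A real difference could also be masked. Unlike sampling error, this component would not shrink with more participants.

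**Working it through.** The document has no figure of its own to reproduce: it gives no BMI distribution, no type mix and no calculation behind 30 per group. What follows is an illustration on stated assumptions.

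**Inputs from the protocol article:** limit of 30 for type 2 only; no limit for type 1 or for the comparison group; 30 per group.

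**Assumptions:** BMI is Normal with mean m and SD s, the same underlying distribution in both groups; a share q of the diabetes group is type 2. Central case m = 28, s = 5; range m = 26 to 29, s = 4 to 5, q = 0.25 to 1.

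**Step 1, truncated mean.** With b = (30 − m)/s, the mean below 30 is m − s·φ(b)/Φ(b). For m = 28, s = 5: b = 0.4, φ(b) = 0.368, Φ(b) = 0.655. The mean is 28 − 5 × 0.562 = 25.19, with SD 3.39. The share at or above 30 is 1 − 0.655 = 34.5%.

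**Step 2, induced difference** (diabetes minus comparison) = −q × (28 − 25.19) = −2.81q.

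**Step 3, yardstick.** The 95% half-width of a 30 v 30 difference is 1.96 × √(v/30 + 25/30), where v is the variance of the mixed diabetes group.

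| Share type 2 | Induced difference (kg/m²) | In SDs | 95% half-width |
|---|---|---|---|
| 25% | −0.70 | −0.14 | 2.48 |
| 50% | −1.40 | −0.28 | 2.41 |
| 75% | −2.11 | −0.42 | 2.30 |
| 100% | −2.81 | −0.56 | 2.16 |

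Over the whole range the difference runs from −0.3 to −3.4 kg/m² and the half-width from 1.7 to 2.5. The share of the comparison group at or above 30 runs from 16% to 42%. In the central case the shift exceeds the half-width only when nearly all the diabetes group is type 2.

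**Step 4, limiting the comparison group alone.** With half type 2, the diabetes mean is 0.5 × 25.19 + 0.5 × 28 = 26.60. Comparators limited to below 30 average 25.19. The difference becomes +1.4, the same size with the opposite sign, because type 1 participants remain unrestricted.

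**Step 5, restricting both groups.** Everyone in the table then has BMI below 30, so under these assumptions both means are 25.19 and the induced difference is 0. The numbers lost are 0.345 × 30 ≈ 10 comparators and, with a half-and-half mix, 0.345 × 15 ≈ 5 type 1 participants. That leaves about 25 v 20. For a measure whose SD is unchanged by the restriction, the interval widens by √(1/25 + 1/20)/√(2/30) = 0.300/0.258 = 1.16, or about 16%.

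**The case against.** The strongest reply is that the document defines its diabetes population deliberately, as type 1 plus non-obese type 2, and may describe it beside mildly frail people without diabetes. The Background also says that long-term insulin treatment is associated with weight gain. Body size may therefore be partly a consequence of the exposure, and equalising BMI could remove part of what is to be described. This stands as a reason to keep the full tables. It does not make the full tables a clean comparison of people with and without diabetes.

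Other points also stand. The component is descriptive, height and weight are measured in all 60 so an imbalance will be visible, and with few type 2 participants the shift is small beside sampling error. Figure 1 is not shown and its legend defines BMI, so a criterion stated there cannot be checked; the written criteria for the non-diabetes group contain none.

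A reader might infer that the diabetes group will certainly look leaner, fitter or better in its lipids. The documents do not support that. It depends on the unknown type mix and on equal underlying BMI; if people with diabetes would otherwise be heavier, the rule could instead offset a real difference. Nor does it follow that the limit itself is wrong, since it has a stated reason within the diabetes group.

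**Conclusion.** The point holds as a limit on interpretation, of minor to moderate weight. The one-sided BMI rule is in the text, and the comparison it affects is a stated aim. The direction and size of the observed difference are not determined by the document. The illustrative shift of about −0.7 to −2.8 kg/m² rests on an assumed Normal(28, 5) distribution, equal underlying BMI and a type 2 share between 25% and 100%. It would be zero if no type 2 participants enrolled.

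A reader might extend the concern to the trial itself. That is not supported: both randomised arms come from the diabetes group under the same criteria, and the recruitment, attrition and attendance criteria do not depend on the comparison group's BMI.

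**What to change.** In Quantitative analysis, add that:

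- the baseline comparison will be reported twice, in full (30 v 30) and restricted to baseline BMI below 30 in both groups, dropping type 1 participants and comparators at or above 30 alike;
- BMI will be shown by group and by diabetes type;
- any statement about body-size-related differences between people with and without diabetes will rest on the restricted table.

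Do not add a BMI limit for the comparison group alone: with type 1 unrestricted, the artefact would change sign.

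The cost is a few lines of analysis wording and no new data. The restricted table is smaller: under the central assumption it loses about 10 of 30 comparators and about a third of type 1 participants (about 5 of 15 with a half-and-half mix). Intervals are then wider for measures whose spread the restriction does not reduce. It also describes only people below BMI 30, so the full tables should stay beside it.
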